## Abstract

**Background:**

An education self-management program for people with osteoarthritis (OA) of the knee was designed to be delivered by health professionals, incorporating their knowledge and expertise. Improvement in quality of life, health status and pain in response to this program has previously been demonstrated in an uncontrolled pilot study. To more rigorously test the effectiveness of the program we will undertake a randomised controlled trial of people with OA of the knee offering specific self-administered exercises and education, in accordance with the principles of self-management.

Aim: To determine whether an education self management program for subjects with Osteoarthritis (OA) of the knee (OAK program) implemented by health professionals in a primary health care setting can achieve and maintain clinically meaningful improvements compared standard medical management in a control group.

**Methods:**

The effects of standard medical management will be compared with the effects of the OAK program in a single-blind randomized study.

*Participants: *146 male and female participants with established OA knee will be recruited. Volunteers with coexistent inflammatory joint disease or serious co-morbidities will be excluded.

*Interventions: *Participants will be randomized into either intervention or control groups (delayed start). The intervention group will complete the OA knee program and both groups will be followed for 6 months.

*Measurements: *Assessments will be at baseline, 8 weeks and 6 months. SF-36, WOMAC and VAS pain questionnaires will be completed. Isometric quadriceps and hamstring strength will be measured using a dynamometer; knee range of movement using a goniometer; and physical function will be determined by a modified timed up and go test. Data will be analysed using repeated measures ANOVA.

**Discussion:**

While there is evidence to support the effectiveness of SM programs for people with hypertension, diabetes and asthma, the evidence available for treatment of arthritis remains equivocal. The aim of this study is to determine the effectiveness of a disease specific self-management program for people with OA knee.

The study design includes all the important features of a clinical experimental study to minimize bias so the results of the study will provide a high level of evidence. People with OA of the knee have identified pain and problems with daily activities as the most important problems associated with their condition. The outcome measures selected specifically address these issues and have demonstrated validity and are responsive within the range of change expected in response to the intervention. Hence the results of the study will reflect their priorities.

The results of the study will provide evidence to guide clinicians and funding bodies seeking to establish priorities regarding the provision of this disease specific program.

**Trial registration:**

ACTR number: 12607000080426

## Background

Self-management is a primary care intervention that has become a popular component of management in a number of chronic conditions including arthritis. Unlike traditional patient education programs, self-management programs aim to achieve more than the provision of information to increase knowledge. They also aim to change health behavior and health status, teaching patients to identify and solve problems, set goals and plan actions [1].

Numerous self-management programs have been developed for different health conditions. Various models have been employed including individual and group-based programs that may be disease specific or generic [2]. Face-to-face interaction with health professionals is an important component of some programs, whereas trained lay leaders, usually presenting scripted information, deliver others.

There is a considerable body of research evaluating self-management programs. Reviews and meta-analyses [3,4] have shown that patient self-management education programs can significantly improve knowledge, compliance behaviours, and health outcomes, however the effectiveness differs between programs and disease states.

One systematic review of self-management interventions for a number of chronic diseases, found a trend towards a small benefit from arthritis programs, but the results were not significant and there was a suggestion of publication bias [2]. Many of the existing arthritis self-management programs are designed to cater for participants with any form of arthritis. Examples of this approach are the Chronic Diseases and Arthritis Self-Management programs (ASMP) developed at Stanford University [5,6]. These programs are also delivered in a group setting but they are led by trained lay tutors. They have a more generic approach as they are catering for participants with a variety of different musculoskeletal diseases in the one group. This approach may be cheaper to deliver but cost-effectiveness is yet to be established [7,8].

The ASMP has been tested widely with the majority of studies conducted in the USA or UK. Many, but not all of these studies have found the program to be effective. Overall, Warsi et al (2004), in their systematic review of self-management interventions for various chronic diseases, found a trend towards a small benefit from arthritis programs, the majority being ASMP or ASMP derivatives, but the results were not significant and here too it was suggested that there was publication bias [2].

We hypothesised that a program designed for a specific diagnostic group may be more effective. We considered a program of this nature would be justified for more prevalent conditions such as osteoarthritis of the knee.

Accordingly, we developed a self-management program for people with osteoarthritis of the knee. The program was designed to be delivered by health professionals. Strategies for pain management; the benefits of different types of exercise (strength, aerobic, flexibility, balance); and approaches for falls prevention were included. In keeping with a social cognitive theory approach, individual problem identification, goal setting and action planning were encouraged to facilitate improvements in self-efficacy. This program was tested in an uncontrolled quality assurance study. The results indicated improvement in pain, quality of life and physical function [9]. The purpose this study was to more rigorously test the program in a randomized controlled study.

## Methods

### Aim

To compare the effectiveness of an osteoarthritis of the knee self-management education program delivered by health professionals with a control group, as determined by improvements in pain, quality of life and physical function.

### Study Design

A two group randomized, controlled repeated measures study design will compare the osteoarthritis of the knee program (OAK) with a similar group of control participants. Independently of the study all participants will be able to receive standard medical management of OA knee. In addition, the intervention group will participate in a disease specific knee osteoarthritis self-management program (OAK). Blinding of participants will not be possible due to the nature of the intervention; however, assessors will be blinded to group allocation. The OAK program will be conducted in a community setting at Arthritis Western Australia.

### Hypothesis

People with osteoarthritis of the knee who complete the OAK Program will report improved quality of life, improved knee function and decreased pain compared with those managed conventionally.

### Ethical Issues

This study has been approved by the Human Research Ethics Committee at Curtin University of Technology (HR141, 2002). All participants will provide written informed consent prior to randomisation. Data access and storage will be in keeping with National Health and Medical Research Council guidelines, as approved. License agreements have been obtained for SF-36 Questionnaire and WOMAC Questionnaire. This trial is registered with the Australian and New Zealand Clinical Trial Registry, number: 12607000080426.

### Subjects

146 participants with established OA of one or both knees will be recruited into the study. As the OAK program is generally provided as a clinical service, subjects will be recruited from among people presenting to enroll in the OAK program. The operational definition for OA knee is diagnosis by a medical practitioner based on either clinical examination or radiological evidence. Disease severity is not a selection criterion. Exclusion criteria will be rheumatoid arthritis or other inflammatory joint disease; knee surgery planned within 6 months of commencing the study; physical impairments that preclude full participation; inability to communicate in English within a group setting or aged ≤ 18 years (Table 1). During the recruitment phase the program will be actively promoted to general practitioners and rheumatologists through professional societies, and to the general public through advertising and media coverage.

**Table 1 T1:** Eligibility criteria

**Inclusion criteria**	**Exclusion criteria**
English speaking	Co-existing inflammatory arthritis
Aged 18 years or over	Serious co-morbidity
Diagnosis of OA (X-Ray or clinical Dx)	Scheduled knee replacement in < 6 months
Referral from GP or Specialist	Cannot meet program time-points
Able to meet program requirements	

Volunteers for the study will be randomized to an intervention group (immediate start) or a control group (delayed start). As there is evidence that SM is an effective addition to usual care [5,10], all volunteers randomized to the control group will be offered the intervention at the completion of the 6-month control period.

### Group allocation

Volunteers will be randomized in blocks to ensure manageable numbers for intervention groups. Pre-prepared cards indicating group assignment will be placed in sealed opaque envelopes and drawn as a lottery by a third party for allocation to treatment groups. In order to ensure optimum group sizes, allocation will not take place until a whole block has been recruited

### Intervention

The OAK program will be conducted over a 6-week period enabling participants to incorporate and consolidate information learned from week to week. In addition to the weekly sessions, participants will be given printed information relevant to the course component discussed each week. Program leaders will be health professionals including nurses, physiotherapists, and occupational therapists that have the knowledge and skills to present information on disease specific topics and accurately respond to complex questions. It is necessary that health professionals who deliver this program meet minimum musculoskeletal knowledge requirements. The fidelity of the OAK program will be maintained by the use of a facilitator's manual with modules for program delivery each week.

To facilitate optimum group dynamics, the target group size will be 12 participants, although this may vary from 8 to 16 depending on recruitment and randomisation. The program approach is holistic and will not exclusively focus on one aspect of care. Self-management constructs will be employed to promote behavioral changes that will be aimed at optimizing participants' health status. Goal setting and the development of strategies to achieve these goals long term [11] will be emphasized in the program. Participants will be encouraged to set their own goals related to health areas that they identify as requiring improvement.

Topics that will be covered in the weekly sessions include:

• Pain management strategies (cognitive and pharmaceutical)

• Joint protection

• Fitness/exercise

• Correct use of analgesia/medications

• Balance/falls prevention/proprioception

• Cognitive techniques

• Pathophysiology

• Nutrition/weight control

• Self-management skills

• Team approach to health care

• SMART goals (**S**pecific, **M**easurable, **A**chievable, **R**ealistic, **T**ime-framed)

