### Statistical Power Calculation

A priori power calculations for this study will be based on the quality of life outcome as measured by the SF-36. Sample size was calculated according to guidelines in the SF-36 Users Manual to determine differences in changes over time between the intervention and control groups using a repeated measures design allowing an inter temporal correlation between scores of 0.60 [16]. The pilot study SF-36 data showed an average improvement of 10 points across the eight domains measured. Assuming this level of improvement is achieved in the intervention group and there is no change in the control group and allowing for a 10% drop out rate, the number of participants required per group will be 60 [16]. In the pilot study, there was a drop out rate of 5% over 3 years, so allowing 10% is a conservative estimate. Differences in changes in functional ability measured using the WOMAC, similar in magnitude to those previously documented [24] would also be detectable in a sample of this size.

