### Data Analysis

Data will be analyzed in a blinded manner. Treatment groups will be examined for comparability at baseline. Main comparisons between treatment groups will be performed using an intention to treat analysis. To test the effects of treatment, between group differences in changes over time will be examined using repeated measures ANOVA. Separate analysis will be conducted for each outcome variable. Statistical significance will be inferred at a 2-tailed p < 0.05. Results will not be adjusted for multiple comparisons as all outcomes of interest have been nominated a priori and such adjustment would likely render all findings of interest, despite their clinical importance, non-significant.

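### The OAK arm is taught in about 5 or 6 classes, but the stated ANOVA and the 60 per group treat classmates as independent; if the class ICC is above zero, the 5% test is liberal

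*Protocol article*

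**What the plan says.** All references are to the Protocol article.

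- **Group allocation.** Individuals are allocated, but with class formation in mind: "Volunteers will be randomized in blocks to ensure manageable numbers for intervention groups". Allocation waits until a block is full.
- **Intervention.** OAK runs over six weeks in weekly sessions led by health professionals. On class size: "the target group size will be 12 participants, although this may vary from 8 to 16 depending on recruitment and randomisation". The reason given for that size is "To facilitate optimum group dynamics".
- **Subjects.** Controls are not taught during follow-up: "all volunteers randomized to the control group will be offered the intervention at the completion of the 6-month control period". Planned recruitment is 146.
- **Statistical Power Calculation.** The inputs are a 10-point SF-36 improvement against no change, a correlation of 0.60 between a person's repeated scores, and 10% dropout. The result: "the number of participants required per group will be 60". No design effect or class ICC is mentioned.
- **Data Analysis.** "between group differences in changes over time will be examined using repeated measures ANOVA", separately for each outcome, with no class or leader term named. "Statistical significance will be inferred at a 2-tailed p < 0.05", without adjustment for multiple comparisons.

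**The concern.** People taught together for six weeks share leaders, discussion and peers. The protocol sizes the classes with group dynamics in mind, so it treats that interaction as part of the treatment. Changes in outcome may then be more alike within a class than between classes. Only the OAK arm is exposed to this, which makes the design partially nested.

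An ANOVA whose only dependence is within person over time treats 60 to 73 OAK participants as that many independent observations, although they sit in only 5 or 6 classes. One unusually good or poor class can shift the arm mean by more than the ANOVA allows for. Two things are at stake: the error rate of every unadjusted test, and whether 60 per group is enough for the stated aim.

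**Working it through.** **The plan's own figure.** Neither power nor SD is stated, so 60 cannot be reproduced; it can only be back-solved. After 10% dropout, 60 × 0.9 = 54 are analysed per group. The SD of change that fits is 10 × √(54/2) / (1.96 + z), and the cross-sectional SD is that value divided by √(2 × (1 − 0.60)).

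- 80% power: 51.96 / 2.80 = 18.55, cross-sectional SD 20.7.
- 90% power: 51.96 / 3.24 = 16.03, cross-sectional SD 17.9.

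Both are possible. At either SD, 60 is what independence requires, with no room for a design effect.

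**Number of classes.** At 12 per class, 60/12 = 5 and 73/12 = 6.1. Across the 8 to 16 range it is about 4 (60/16) to 9 (73/8).

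**Effect of clustering in one arm.** Assumptions: a class ICC of 0.01 to 0.10 for the change in outcome, m = 12 per class, 1:1 allocation, and 80% power for 60 per group under independence.

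- OAK design effect: DE = 1 + (m − 1) × ICC.
- Variance of the group difference is multiplied by f = (1 + DE)/2.
- True error of the nominal 5% test: 2 × (1 − Φ(1.96/√f)).
- Number needed: 54 × f, then divided by 0.9.
- Power with n recruited per arm: Φ(2.80 × √((n/60)/f) − 1.96).

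| ICC | DE | f | √f | True error | 60 becomes | Power, 60 per arm | Power, 73 per arm |
|---|---|---|---|---|---|---|---|
| 0.01 | 1.11 | 1.055 | 1.03 | 5.6% | 63-64 | 78% | 85% |
| 0.02 | 1.22 | 1.11 | 1.05 | 6.3% | 67 | 76% | 84% |
| 0.05 | 1.55 | 1.275 | 1.13 | 8.3% | 77 | 70% | 78% |
| 0.10 | 2.10 | 1.55 | 1.25 | 11.5% | 93-94 | 61% | 70% |

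The ranges in the sixth column reflect when rounding is done. For example, 60 × 1.55 = 93.0, but 54 × 1.55 = 83.7, rounded to 84, and 84/0.9 = 93.3, rounded to 94.

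A simulation of 20,000 trials with 5 or 6 classes of 12 gave error rates of 5.7-5.8%, 6.1-6.6%, 8.1-8.6% and 11.6-11.8%.

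**What 146 covers.** 73/60 = 1.217. Setting f = 1.217 gives ICC = 2 × 0.217/(m − 1), which is about 0.06 at m = 8, 0.04 at m = 12 and 0.03 at m = 16.

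**Sensitivity.**

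- Class size at ICC 0.05: the number needed is 72 at m = 8 and 84 at m = 16, and the true error is 7.1% and 9.5%.
- Dropout: if 10% dropout leaves 10.8 per class, then at ICC 0.05 f = (1 + 1.49)/2 = 1.245, the true error is 7.9%, the number needed is about 75, and the power with 146 is 79%.
- Base power: if 60 gave 90% power, 146 keep about 89% at ICC 0.05.

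**Cost of the corrected test.** A class-level Satterthwaite test with 5 or 6 classes brings the simulated error back to about 5% to 5.6%. The typical (median) interval is then about 8-10% wider than the ANOVA's at ICC 0.02 and 17-19% wider at ICC 0.05. Widths vary from trial to trial and are skewed. Putting the expected variances into the formula at ICC 0.05 and 5 classes gives df = 2.55² / (1.55²/4 + 1/59) = 10.5, and widening of 1.129 × 2.21/1.98 = 1.26. With 6 classes df is 13.1 and widening 1.23.

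**The case against.** - **The ICC may be close to zero.** The Intervention section provides a facilitator's manual with weekly modules, minimum knowledge requirements for leaders, and goals set by each participant. All of these would limit differences between classes. This stands as to size: at 0.01 the effect is minor. It does not remove peer interaction, and the stated analysis in effect sets the ICC to zero.
- **The plan recruits 146, not 120.** This stands for power. A reader might infer from the 60 that the trial is underpowered; the document does not support that, because 146 cover an ICC up to about 0.04 at 12 per class. Nor does it say that the extra 26 were meant for clustering. A larger sample does not correct the error rate of an ANOVA without a class term.
- **Recruitment blocks matter too.** The natural reading of Group allocation is that each block supplies a class and concurrent controls. Variation shared by a block would largely cancel between arms, and ignoring it would make the ANOVA somewhat conservative, partly offsetting the liberality. This stands as a limit on the error figures, which leave blocks out, and the replacement model should include the block.
- **A statistical analysis plan may deal with this.** Random effects and degrees of freedom are commonly set there, and one not shown could add a class term. But this article names the test and states the required number, both without allowance for class. The point is about what is stated.

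**Conclusion.** The point holds conditionally. With teaching in classes in one arm only, the stated ANOVA gives standard errors that are too small for any positive class ICC, apart from any offset from shared block variation. The true error of the 5% test is about 5.6% to 11.5% over an assumed ICC of 0.01 to 0.10 at 12 per class, and slightly less if dropout shrinks the classes. The stated 60 per group is understated by about 3 to 34 over the same range.

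A reader might go further and take it as established that every standard error is materially wrong. The document gives no ICC, so that cannot be said; the harm runs from negligible to material. The power figures also rest on an 80% base and a 1:1 ratio, neither of which is stated, and on a normal approximation that is a little optimistic with so few classes. Severity: should-fix, conditional on the ICC.

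**What to change.** 1. Record class and leader for every OAK participant, and the recruitment block for everyone. Programme attendance is already collected, so the added data are small and easiest to capture as classes form.
2. Replace the ANOVA with a mixed model for the repeated measures that has a random class effect in the OAK arm only, accounts for the recruitment block, and uses Satterthwaite or Kenward-Roger degrees of freedom.
3. Restate the power for the planned 146 over a range of ICCs, giving the assumed SD, base power and allocation ratio.

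The cost is analysis wording, a few data fields and a restated power figure, with no extra patients. The downside is real: a class variance estimated from 5 or 6 classes is imprecise, and intervals will be wider by the amounts shown in the working. If the ICC is above about 0.04 at 12 per class, the restated power for 146 will fall below the level assumed for 60, and the plan should say so.

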### Assessments and Procedures

Assessments will be performed by 2 physiotherapists blinded to group allocation; conducted one week prior to the first self-management session (baseline) and on the week following the sixth and final session (week 8). The physiotherapists performing assessments will have no contact with the participants other than during the assessment sessions and will not participate in facilitation of the program. Participants will be assessed by the same physiotherapist whenever possible to ensure consistency.

Members of the control group will also attend assessments at baseline, and week 8. All volunteers will be assessed again 6 months after randomisation. In keeping with intention to treat principles, all participants will be encouraged to attend for follow-up measurements regardless of level of attendance at the self-management intervention. Self reported questionnaires (WOMAC, SF-36, VAS pain) would be mailed out to participants that are unable to attend assessment visits. Program and assessment attendance (at all time-points) will also be collected and collated.

Demographic information will include age, sex, co-morbidities and socioeconomic information. Socio-economic scales will be compiled using "The Index of Relative Socio-Economic Disadvantage" scales [12]. This index provides a weighted value that includes variables that reflect or measure disadvantage. These variables include: low-income, low educational attainment, high unemployment and low skilled occupations.

The dependent variables for the study are listed below.

